### 5.6.3 Safety outcomes

Safety assessments will consist of incidence and frequency of adverse events (AEs) and serious AEs during the trial period, the evaluation of application site tolerability, clinical laboratory parameters (complete blood count, urinalysis, hepatic and renal functions), vital signs (heart rate, body temperature, respiratory rate and blood pressure), and physical examinations at week 0, week 8 and week 20. Each patient with an adverse event will be counted only once for each Medical Dictionary for Regulatory Activities (MedDRA), version 22.0, preferred term [52]. The severity of AEs will be based on the Common Terminology Criteria for Adverse Events, version 5.0 [53]. The WHO-UMC system will be used for standardised case causality assessment [54]. Serious AEs should be reported to the GPHCM Ethics administration within 24 hours and be recorded in the serious AEs form.

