| Outcomes           | 
Trial feasibility
 
 
• The proportion of involvement by the number of screened, eligible and consenting participants, as well as the time requirement to recruit eligible participants will be used to assess the feasibility of the study setting, eligible criteria and recruitment strategies
 
• The compliance rate of using trial medications and the acceptability question will be used to quantitatively evaluate the feasibility and acceptability of the trial
 
• Blinding credibility at week 4, week 8 and week 20
 
• Determine the primary outcome and provide data for sample size calculation in the full-scale trial
 
 
Efficacy outcomes
 
 
• Primary outcome 
 
✓ The mean change in the PASI from baseline to week 8 and week 20
 
 
 
• Secondary efficacy outcomes 
 
✓ The PGA response, defined as a PGA score of 0 (clear) or 1 (almost clear) and a decrease from baseline at least 2 points on the 7-point static PGA at week 8 and week 20
 
✓ The percentage of patients who achieve PASI-75 at week 8 and week 20
 
✓ The percentage of patients who achieve PASI-50 at week 8 and week 20
 
✓ The mean change in the percentage of total BSA affected by psoriasis from baseline to week 8 and week 20
 
✓ The mean change in the itch VAS from baseline to week 8 and week 20
 
✓ The mean change in the DLQI from baseline to week 8 and week 20
 
✓ The mean change in the Skindex-16 from baseline to week 8 and week 20
 
✓ The relapse rate at week 20, defined as a loss of 50% of PASI improvement from baseline in patients who achieve PASI-50 at week 8
 
 
 
 
Safety outcomes
 
 
✓ The incidence and frequency of adverse events (AEs) and serious AEs during the trial period
 
✓ Chemical examinations (complete blood count, urinalysis, hepatic and renal
 
 |

|                   |                                                                                                                                                                                                            |

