#### 5.3.1.1 Administration instructions

One packaged of FZHFZY granules will dissolve in warm water at 35°C to 38°C. The amount of

water will be adjusted according to the size of the bathtub and the location of the skin lesion. Participants will be instructed to adjust their bathing position to ensure the psoriasis lesions will be soaked by the liquid. The height of liquid should not exceed the chest when a patient is in a semi-recumbent or sitting position if a whole-body bath is required. Where a whole-body bath is not needed, patients may reduce the amount CHM/placebo granule and water according to doctor's instruction. The bathing duration is between 15 and 20 minutes once a day for eight weeks at home.

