#### 5.3.5 Trial duration

The trial period is 20 weeks, including an 8-week treatment phase and a 12-week follow-up phase.

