##### 5.4.1.2 Outcome measures and visits

- PASI, BSA, sPGA and itch VAS: Participants will be evaluated these measures at week 0, 2, 4, 6, 8, 12, 16 and 20
- DLQI and Skindex-16: Evaluate these measures at week 0, 8, and 20
- 11-point ordinal scale: Evaluate it at week 8 and 20
- Blinding credibility: Evaluate it at week 8 and 20
- Chemical examinations: Evaluate electrocardiograms at the baseline, and collect blood (two 4 ml-EDTA tubes and two drying tubes) and urine (one 10 ml-urine tube) at week 0, 8 and 20
- Photos taken for representative skin lesions: Conduct it at each visit
- Concomitant medication, and AEs: Record it during the whole trial phase

- Dispense and collect trial drugs: Dispense trial drugs at week 0, 2, 4, and 6; collect trial drugs at week 2, 4, 6 and 8
- Dispense and collect home diary record sheet: Dispense it at week 0, 2, 4, 6, 8, 12, and 16; collect it at week 2, 4, 6, 8, 12, 16 and 20

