## 5.7 Pre-assessment and disposal plan of relevant risks

### 5.7.1 Adverse reaction of CHM bath therapy

The common adverse reaction of CHM bath therapy is skin irritation (e.g. skin erythema, itching), chest tightness and shortness of breath. These symptoms may disappear if participants stop the bathing immediately. If participants suffer from any unexpected condition no matter whether it is related to the trial medications or not, they can contact the researcher immediately for further suggestions.

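### The adverse-event outcome pools 8 weeks on treatment with 12 weeks off treatment in one count per preferred term, which can weaken the between-arm safety comparison; report it by phase as well

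*Protocol*

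**What the plan says.** Section 5.6.3 states: "Safety assessments will consist of incidence and frequency of adverse events (AEs) and serious AEs during the trial period". The synopsis gives the same window: "The incidence and frequency of adverse events (AEs) and serious AEs during the trial period". Section 5.3.5 defines its length: "The trial period is 20 weeks, including an 8-week treatment phase and a 12-week follow-up phase". Exposure to the granules is shorter. Section 5.3.1.1 says "The bathing duration is between 15 and 20 minutes once a day for eight weeks at home", and Table 1 shows trial drugs collected for the last time at week 8.

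Recording runs throughout (5.4.1.2): "Concomitant medication, and AEs: Record it during the whole trial phase". The counting rule in 5.6.3 is "Each patient with an adverse event will be counted only once for each Medical Dictionary for Regulatory Activities (MedDRA), version 22.0, preferred term".

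On what to expect from the bath, 5.7.1 says "The common adverse reaction of CHM bath therapy is skin irritation (e.g. skin erythema, itching), chest tightness and shortness of breath", and then "These symptoms may disappear if participants stop the bathing immediately".

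Three other places bear on the point:
- Section 5.6.2 reports efficacy at week 8 and week 20 separately and measures relapse at week 20.
- Section 5.3.4 recognises itch as a symptom of psoriasis.
- Section 5.6.3 also lists an evaluation of application-site tolerability and uses the WHO-UMC system for causality.

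The protocol does not define an on-treatment window for adverse events. It also does not say whether worsening or return of psoriasis is itself an adverse event.

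**The concern.** A preliminary estimate of the add-on safety of FZHFZY is a stated aim (3.1) and will inform the full-scale trial. The reactions named in 5.7.1 are expected while patients are bathing and may resolve when they stop. Any effect of the bath on these terms should therefore show mainly in weeks 0 to 8. The outcome as written adds 12 weeks in which neither arm is treated and reports one proportion per term.

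Two things can follow. Follow-up events of the same term that are equally common in both arms narrow the contrast between arms. And erythema and itching are also features of psoriasis. If its return is written down as an adverse event, and the arms relapse at different rates, the 20-week comparison mixes tolerability of the bath with durability of its effect. With about 30 patients per arm there is little signal to spare.

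**Working it through.** **Inputs from the protocol.** Treatment 8 weeks, follow-up 12 weeks, total 20 (5.3.5). One count per patient per preferred term (5.6.3). 60 patients randomised 1:1 (5.2), so 30 per arm. Two-sided 5% level (5.9.2). The protocol gives no adverse-event rate and no safety power, so there is no safety figure to reproduce. The sample size does reproduce: 50/(1 - 0.15) = 58.8, rounded up to 59, against 60 stated.

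**Share of the window off treatment.** 12/20 = 60%.

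**Equal follow-up events.** For one preferred term let p be the proportion with onset on treatment. Let b be the proportion with onset in weeks 8 to 20, independent of p and equal in both arms. Then

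20-week proportion = 1 - (1 - p)(1 - b)

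and the difference between arms is

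(p_FZHFZY - p_placebo)(1 - b).

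With p assumed to be 20% v 5%, 30 per arm (SE is that of the difference; power uses a normal approximation):

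| b | FZHFZY v placebo | Difference (points) | SE (points) | Ratio | Power |
|---|---|---|---|---|---|
| 0 | 20.0% v 5.0% | 15.0 | 8.3 | 4.00 | 0.417 |
| 10% | 28.0% v 14.5% | 13.5 | 10.4 | 1.93 | 0.245 |
| 20% | 36.0% v 24.0% | 12.0 | 11.7 | 1.50 | 0.170 |
| 30% | 44.0% v 33.5% | 10.5 | 12.5 | 1.31 | 0.129 |
| 50% | 60.0% v 52.5% | 7.5 | 12.8 | 1.14 | 0.084 |

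The FZHFZY and placebo proportions only rise as b grows. The difference shrinks while its standard error grows. With b = 0 nothing changes. Starting from 30% v 10%, b = 30% takes the difference from 20.0 to 14.0 points and the ratio from 3.0 to 1.38.

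**The same effect with weekly rates.** Take a background rate in both arms for 20 weeks and an added rate on FZHFZY for 8 weeks, with incidence = 1 - exp(-rate x weeks).

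- Background 2%, added 5% per week. To week 8: 1 - exp(-0.56) = 42.9% v 1 - exp(-0.16) = 14.8%. To week 20: 1 - exp(-0.80) = 55.1% v 1 - exp(-0.40) = 33.0%. The difference goes from 28 to 22 points, the ratio from 2.9 to 1.7, and exact power of Fisher's test from 0.59 to 0.31.
- Background 1%, added 5%: the difference goes from 30 to 27 points.
- Background 0.2%, added 2%: the difference goes from 14.6 to 14.2 points.
- Across backgrounds of 1 to 4% and added rates of 3 to 5%, ratios of 1.6 to 5.0 become 1.2 to 2.5.

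**Follow-up events that differ by arm.** This applies only if relapse symptoms are recorded as adverse events. With 20% v 5% on treatment:

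- Follow-up 10% (FZHFZY) v 30% (placebo): 1 - 0.80 x 0.90 = 28.0% v 1 - 0.95 x 0.70 = 33.5%. The sign reverses.
- Follow-up 30% v 10%: 1 - 0.80 x 0.70 = 44.0% v 1 - 0.95 x 0.90 = 14.5%. The difference grows to 29.5 points.

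So the distortion can go either way.

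**The case against.** The strongest reply is that splitting adverse-event tables by phase is ordinary analysis-plan detail, and that the analysis plan is not shown. Nothing in the cited sections is contradictory. Collecting events to week 20 is sound, and week 8 is a visit, so events can be assigned to a phase later. That largely stands. What remains is that 5.6.3 and the synopsis do more than set a surveillance period. They fix an outcome, its window and a counting rule, and followed as written they pool exposed and unexposed time.

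A reader might infer that bath reactions are lost or diluted out of the count. They are not: a cumulative proportion per patient cannot fall. Because counting is by preferred term, unrelated follow-up events such as a cold do not touch the term for itch or erythema. Only the same term in follow-up matters.

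A reader might also infer that returning psoriasis will mask bath irritation. The protocol does not support that as a prediction. It captures return of disease as efficacy (relapse, PASI, itch VAS) and does not say that it is also recorded as an adverse event. Masking further needs relapse to differ by arm in the right direction.

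Nor is the incidence count the only safeguard. Application-site tolerability and WHO-UMC causality are both in 5.6.3. They help only in part. Tolerability has no clearly separate window, the incidence outcome is not limited to causally related events, and causality is hard to judge when the reaction resembles the disease.

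Finally, power is a weak yardstick in a pilot with no formal sample-size calculation. The risk difference, which moves less than the ratio, is the fairer measure.

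**Conclusion.** The point holds as a limited one. The stated outcome combines 8 weeks of treatment with 12 weeks off treatment, and one count per preferred term does not tell the two apart. Follow-up events of the same term, equal in both arms, multiply the risk difference by (1-b). That ranges from negligible (14.6 to 14.2 points at a very low background) through modest (28 to 22 points) to a halving at b = 50%. Reversal of the contrast is possible but conditional on relapse being recorded as an adverse event and differing by arm, which the protocol leaves open.

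All event rates here are assumptions, as is the independence of on-treatment and follow-up events. The protocol's own figures are not in error, and 20-week collection should not be shortened. The change is worth making because it costs little and because preliminary safety is one of the trial's aims.

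**What to change.** Keep collection of adverse events and serious adverse events to week 20. In 5.6.3 and the synopsis:

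- Report incidence by arm for events with onset from the first bath to the week 8 visit, and name this as the comparison used to judge the safety of the bath.
- Report events with onset after week 8 to week 20 separately, and keep the 20-week total beside them.
- Apply the once-per-preferred-term rule within each phase. A patient may then appear in both phase columns, so the two need not add up to the total.
- State whether worsening or return of psoriasis is recorded as an adverse event or only as an efficacy outcome.

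The cost is a few sentences, two extra table columns and use of the onset date. No extra visits or patients are needed.

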## 5.7 Pre-assessment and disposal plan of relevant risks

### 5.7.1 Adverse reaction of CHM bath therapy

The common adverse reaction of CHM bath therapy is skin irritation (e.g. skin erythema, itching), chest tightness and shortness of breath. These symptoms may disappear if participants stop the bathing immediately. If participants suffer from any unexpected condition no matter whether it is related to the trial medications or not, they can contact the researcher immediately for further suggestions.

### 5.7.2 Other types of psoriasis

If participants in the trial are diagnosed with other type psoriasis (erythrodermic psoriasis, psoriatic arthritis, or pustular psoriasis) by researchers, the study will be terminated. They will be treated according to psoriasis clinical guidelines.

## 5.8 Data management

All physicians, assessors and research assistants will attend training workshops before the conduction of the trial. Investigators will be provided with a written protocol and required to follow the standard operating procedures. The quality controllers from the Guangdong International Clinical Research Centre of Chinese Medicine (Guangzhou, China) will undertake the monitoring tasks of the trial. All data will be entered into a pre-designed, password-protected dataset by personnel blinded to group allocation. Data entry will be performed continuously throughout the study using the double-check method, with any correction or changes of written data in participants' case report forms documented and dated. Any information obtained in connection with this research project will be de-identified using unique study codes. A reference table linking the study code to the participant's personal details will be stored separately in a secured filing cabinet. Only study investigators will have access to the information. Research data will be kept secure at the GPHCM and the RMIT University for a minimum of 15 years after publication before being destroyed [55].

## 5.9 Statistical methods

### 5.9.1 Sample size calculation

Since this is a pilot study, a sample size calculation is not performed. The pilot study aims for 60 participants because a pilot study with at least  $n = 50$  is advisable in many circumstances at a high level of confidence [56], considering a 15% loss to follow-up.

### 5.9.2 Quantitative data analysis

Statistical analysis will be performed in a blinded manner by qualified statisticians using PASW Statistics 25.0 (IBM SPSS Inc., Armonk, New York, USA). All statistical tests are two-sided with a  $P$  value of  $<0.05$  being considered statistically significant.

Efficacy analyses will be based on the intention-to-treat (ITT) population and safety analyses will be based on the safety analyses set population, both of them defined as all randomised patients who received at least one dose of study treatment and the data of at least one visit. Missing data will be replaced using the multiple imputation method for ITT analysis. For the outcome variables, continuous data (e.g. mean change in PASI score, BSA, itch VAS, and DLQI) will be summarised as mean and standard deviation (data with normal distribution) or mean and interquartile range (data without normal distribution), and categorical data (e.g. PASI-50, PASI-75, and relapse rate) will be summarised as counts and percentages. The primary analyses for primary and secondary outcome variables will be based on the ITT population approach, using data collected at baseline, week 8 and week 20.

When outcome variables are continuous data, using an independent  $t$ -test (data with normal distribution) or Mann-Whitney  $U$  test (data without normal distribution) compares the difference between two groups. When outcomes variables are categorical data, using the Chi-squared test (total samples  $\geq 40$  and expectation  $\geq 5$ ) or Fisher's exact test (total samples  $<40$  or expectation  $<1$ ) compares the difference between the two groups. The efficacy outcomes will be assessed by a generalised linear mixed model for repeated measures.

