### 3. Aims and objectives

#### 3.1 Aims

The study will assess the feasibility of the trial protocol qualitatively and quantitatively, and preliminary estimate the add-on efficacy and safety of CHM formula FZHFZY external application to topical urea cream for patients with mild-to-moderate psoriasis vulgaris. Results from the pilot study will optimise the study design.

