#### 3.2 Objectives

The pilot trial will have objectives to:

- Assess the feasibility of study setting, eligible criteria, intervention, outcome measurements, participant timeline and recruitment strategies
- Explore the blinding credibility and the acceptability of the trial

- Determine the adequate sample size for a definitive full-scale RCT
- Preliminary estimate the add-on efficacy and safety in the treatment group (FZHFZY+ urea cream) compared to that in the control group (Placebo+ urea cream).
- Obtain detailed qualitative feedback on experience and acceptability of patients who complete the pilot RCT.

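### The pilot sets out to estimate the add-on effect, but the only inferential criterion fixed for the efficacy outcomes is P<0.05, with no between-arm difference or confidence interval named as the result

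*Protocol*

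**What the plan says.** Section 3.1 states the efficacy aim as to "preliminary estimate the add-on efficacy and safety of CHM formula FZHFZY external application to topical urea cream". Section 3.2 makes it a comparison between arms: "Preliminary estimate the add-on efficacy and safety in the treatment group (FZHFZY+ urea cream) compared to that in the control group". Section 5.6.1 adds that the pilot should supply data for sizing the full-scale trial.

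Section 5.9.1 says: "Since this is a pilot study, a sample size calculation is not performed". The total of 60 rests on a rule of thumb that at least 50 participants "is advisable in many circumstances at a high level of confidence", with an allowance for 15% loss to follow-up.

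Section 5.9.2 contains three elements that bear on this point:

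- A significance rule: "All statistical tests are two-sided with a" P value below 0.05 "being considered statistically significant".
- Between-arm tests: t-test or Mann-Whitney for continuous outcomes, chi-squared or Fisher's exact test for categorical outcomes.
- Descriptive and model output: per-arm mean with SD (or mean with interquartile range), counts and percentages, and a generalised linear mixed model for repeated measures on the efficacy outcomes.

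No section names a between-arm mean difference, risk difference or confidence interval as a result to be reported, and none describes the P values as exploratory or descriptive. In section 5.9 the word confidence occurs only in the sample-size rule of thumb.

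**The concern.** An estimation aim calls for an estimate and its uncertainty. The criterion the protocol fixes answers a different question, whether the difference is significant, in a trial that by its own account was not sized by calculation.

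The per-arm summaries do not fill the gap, because the objective in section 3.2 is a contrast between arms. Mann-Whitney, chi-squared and Fisher tests, as named, give a P value and no effect size. For non-normal data the plan pairs a Mann-Whitney P value with a mean and interquartile range, from which a standard interval for the difference cannot be computed directly. The mixed model could give a contrast, but none is specified.

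What is at stake is how the pilot informs the full-scale trial. A moderate add-on effect could come out as non-significant with no planned output showing that the data remain compatible with it. A chance significant result could equally be given too much weight.

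**Working it through.** **Inputs from the protocol.** Total 60, 1:1 allocation (sections 5.2 and 5.9.1); 15% loss and a minimum of 50 (section 5.9.1); two-sided alpha 0.05 (section 5.9.2).

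**Assumptions.** The protocol gives no effect size, SD or response rate. Standardised differences of 0.2 to 0.8 SD and response rates of 20% v 40% are therefore assumed, for illustration. Because 5.9.2 imputes missing data, the effective number per arm is bracketed: 25 (the section 5.9.1 minimum of 50, split equally) to 30 (all randomised).

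**Step 1, the plan's own figure.** 50/(1 - 0.15) = 58.8, rounded up to 59. Checking the other way, 60 x 0.85 = 51, which meets the minimum of 50. The stated 60 reproduces.

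**Step 2, precision for a mean difference.** The 95% half-width in SD units is t(0.975, 2n-2) x sqrt(2/n).

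- n = 25 per arm: 0.569 SD
- n = 30 per arm: 0.517 SD

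**Step 3, power of the planned t-test** (two-sided 0.05, noncentral t).

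| Assumed true difference | 25 per arm | 30 per arm |
|---|---|---|
| 0.2 SD | 11% | 12% |
| 0.3 SD | 18% | 21% |
| 0.5 SD | 41% | 48% |
| 0.8 SD | 79% | 86% |

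At 0.5 SD the chance of a non-significant result is 100 - 41 = 59% with 25 per arm and 100 - 48 = 52% with 30 per arm. The difference detectable with 80% power, (1.96 + 0.84) x sqrt(2/n), is about 0.79 SD and 0.72 SD respectively.

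**Step 4, what a non-significant result would conceal.** Take 51 evaluable, split 26 v 25. The half-width is t(0.975, 49) x sqrt(1/26 + 1/25) = 0.563 SD. A result with P = 0.20 corresponds to an observed difference of 0.364 SD. Its 95% interval is 0.364 - 0.563 = -0.199 to 0.364 + 0.563 = 0.927 SD. Reported as non-significant, it looks like no effect; reported with its interval, it is compatible with anything from a small disadvantage to a large benefit.

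**Step 5, a responder outcome** (assumed 20% v 40%). The half-width is 1.96 x sqrt(0.2 x 0.8/n + 0.4 x 0.6/n).

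- n = 25 per arm: 24.8 percentage points, power 34%
- n = 30 per arm: 22.6 percentage points, power 39%

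The concern does not depend on how many outcomes or visits are tested. It would be the same with one outcome at one visit.

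**The case against.** The best defence has four parts.

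- **The plan is not confined to tests.** A reader might infer that 5.9.2 yields nothing but significant-or-not verdicts. The text does not support that. It plans means, SDs, counts and percentages, from which a raw difference and often an approximate interval could be worked out; the t-test is itself built on the mean difference and its standard error; and the mixed model can give a contrast. This part stands. What it leaves untouched is that none of these is named as the between-arm result, while the significance threshold is fixed.
- **Intervals may be in the statistical analysis plan.** A separate plan, not to hand, may specify them, so the missing interval alone would be no finding. This is fair. The point rests instead on the mismatch between an estimation aim and the one inferential rule the protocol does fix. Adding intervals elsewhere would not change that rule or make the P values descriptive.
- **The 0.05 sentence is only a convention.** The protocol nowhere says that non-significance means no effect, and it does not tie progression to the full-scale trial to a P value. This is correct, so misreading is a risk and not something the protocol instructs. The risk remains because nothing in the protocol tells the reader otherwise.
- **Safety and feasibility.** A reader might extend the point to adverse events and feasibility measures. The documents do not support that: section 5.6.1 names no test for feasibility, section 5.6.3 describes safety by incidence and frequency, and the outcomes given as examples in 5.9.2 are all efficacy measures. That few patients leave a wide interval around an event rate is true of any arm of 30 and shows no fault in this plan.

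The planned SDs and response percentages are also direct inputs for sizing the full-scale trial, so that objective is not left unserved.

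**Conclusion.** The point holds for the efficacy outcomes, in limited form. The protocol states an aim of estimating the add-on effect against control and did no sample size calculation. The only inferential criterion it fixes is two-sided P<0.05, with no between-arm difference or interval named as the result and no statement that P values are exploratory. At 25 to 30 per arm the 95% half-width is about 0.52 to 0.57 SD, and a true effect of 0.5 SD would be missed by the rule in about 52 to 59% of such pilots.

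The half-widths in SD units depend only on the numbers per arm. The power figures rest on assumed effects and the responder figures on assumed rates. With a true effect of 0.8 SD, power is 79 to 86%, so the rule performs badly for small and moderate effects and not for every effect. This should be changed; it does not invalidate the design.

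**What to change.** In section 5.9.2, state that the main result for each efficacy outcome at weeks 8 and 20 is the between-arm difference with a two-sided 95% confidence interval. Use a mean difference for continuous outcomes, taken from the planned mixed model where that model is used, and a risk difference for binary outcomes. Replace the significance sentence with a statement that P values are descriptive and will not be used to claim or to deny an add-on effect.

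The cost is a few sentences and a little more output. Sample size, visits and data collection are unchanged. The one small loss is that the report cannot headline a statistically significant result.

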## 5.5 Termination and withdrawal

If participants are diagnosed with other type psoriasis (erythrodermic psoriasis, psoriatic arthritis, or pustular psoriasis) or suffer from serious adverse events during the trial, the study will be terminated. In addition, participants have the right to withdraw from the study at any time for any reason. Trial investigators can receive feedback on trial medications from these participants and ask them to complete the relevant examinations, which will help the researcher to collect data and benefit the care of participants' health.

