#### 5.6.2.2 Secondary efficacy outcomes

- The PGA response, defined as a PGA score of 0 (clear) or 1 (almost clear) and a decrease from baseline at least 2 points on the 7-point static PGA at week 8 and week 20 respectively [46]
- The percentage of patients who achieve at least 75% improvement in PASI score from baseline (PASI-75) to week 8 and week 20 respectively [47]
- The percentage of patients who achieve at least 50% improvement in PASI score from baseline (pasi-50) to week 8 and week 20 respectively [47]
- The mean change in the percent of total BSA affected by psoriasis from baseline to week 8 and week 20 respectively [45]
- The mean change in the total itch VAS from baseline to week 8 and week 20 respectively [48]
- The mean change in the DLQI total score from baseline to week 8 and week 20 respectively [49]
- The mean change in the Skindex-16 total score from baseline to week 8 and week 20 respectively [50]
- The relapse rate at week 20, defined as loss of 50% of PASI improvement from baseline in patients who achieve PASI-50 at week 8 [51].

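### With multiple imputation as the only missing-data rule, participants removed for another psoriasis type or a serious adverse event can be imputed as PASI-50, PASI-75 or PGA responders

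*Protocol*

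**What the plan says.** Section 5.9.2 states the rule without exception by outcome or by reason: "Missing data will be replaced using the multiple imputation method for ITT analysis". It then sets its scope, with week 20 as the last time point: "The primary analyses for primary and secondary outcome variables will be based on the ITT population approach, using data collected at baseline, week 8 and". PASI-50, PASI-75 and relapse are named there as categorical outcomes. The mixed model mentioned at the end of the section brings no other missing-data rule.

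The responder definitions in section 5.6.2.2 do not mention withdrawal. PASI-75, for example, is only "The percentage of patients who achieve at least 75% improvement in PASI score from baseline (PASI-75) to week 8 and week 20 respectively". The PGA definition is likewise silent. Relapse is counted among those with PASI-50 at week 8.

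Section 5.5 covers participants who develop erythrodermic, pustular or arthritic disease "or suffer from serious adverse events during the trial, the study will be terminated". The wording refers to the study, but the context points to that participant's own participation. Section 5.7.2 repeats the rule for conversion and adds: "They will be treated according to psoriasis clinical guidelines". On data after withdrawal, section 5.5 says only this: "Trial investigators can receive feedback on trial medications from these participants and ask them to complete the relevant examinations". That permits later assessments but does not require PASI or PGA at week 8 or week 20.

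**The concern.** Standard multiple imputation assumes data are missing at random. It fills a missing week-8 or week-20 value as if the participant had continued and behaved like similar participants who stayed. That suits a missed visit. It does not suit a participant taken out because the psoriasis changed to another type or because the treatment was not tolerated. Such a participant has a poor outcome that is known in substance, yet the rule allows a share of the imputed data sets to record a response.

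Relapse is affected as well. A participant removed before week 8 can enter its denominator through an imputed PASI-50, and membership then varies between imputations.

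At stake are the response rates that the pilot hands on. Section 5.6.1 asks the pilot to settle the full-scale trial's primary outcome and to supply data for its sample size, so these rates could be used in planning.

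**Working it through.** **The plan's own figure.** Section 5.9.1 aims for at least 50 participants, "considering a 15% loss to follow-up". 50 / (1 − 0.15) = 58.8, so 59; the planned 60 leaves 60 × 0.85 = 51. The 60 is reproduced and is not in question. At 1:1 it gives 30 per arm.

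**Inputs.** The arm size of 30 comes from the protocol. Response rates pT (FZHFZY) and pC (control) among participants with data, and removed fractions dT and dC, are assumptions.

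**Formulas.** If the imputation model has no informative covariates, a removed participant receives about the arm's observed rate.
- Imputed difference = pT − pC
- Difference with removals as non-response = pT(1 − dT) − pC(1 − dC)
- Shift = pT·dT − pC·dC, which is positive only when dT/dC > pC/pT

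**Results at 40% v 20%.** The imputed difference is 20.0 points in every row, and the break-even dT/dC is 0.20/0.40 = 0.5.

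| Removed, FZHFZY v control | Rates with non-response | Difference | Shift from imputing |
|---|---|---|---|
| 1 v 0 | 38.7% v 20.0% | 18.7 | +1.3 |
| 1 v 1 | 38.7% v 19.3% | 19.3 | +0.7 |
| 2 v 2 | 37.3% v 18.7% | 18.7 | +1.3 |
| 2 v 1 | 37.3% v 19.3% | 18.0 | +2.0 |
| 2 v 0 | 37.3% v 20.0% | 17.3 | +2.7 |
| 1 v 2 | 38.7% v 18.7% | 20.0 | 0.0 |
| 0 v 1 | 40.0% v 19.3% | 20.7 | −0.7 |
| 0 v 2 | 40.0% v 18.7% | 21.3 | −1.3 |

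**Other assumed rates.** For removals of 2 v 0, 2 v 2 and 0 v 2, the shifts are:
- 30% v 15%: +2.0, +1.0 and −1.0 points (break-even 0.5)
- 50% v 30%: +3.3, +1.3 and −2.0 points (break-even 0.6)
- 60% v 40%: +4.0, +1.3 and −2.7 points (break-even 0.67)

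**How often a removed participant becomes a responder.** With two removals in an arm with 40% response, 1 − 0.6² = 64% of imputed data sets contain at least one such responder. At 50% response it is 1 − 0.5² = 75%.

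**If earlier PASI enters the model.** Section 5.4.1.2 schedules PASI at weeks 0, 2, 4, 6, 8, 12, 16 and 20. Assume baseline 7, week-4 mean 5, week-8 mean 4, SD 2.5 and correlation 0.5. PASI-50 then means a week-8 score of 3.5 or less, with marginal probability Φ((3.5 − 4)/2.5) = 0.42. Given a last score x at week 4, the week-8 mean is 4 + 0.5(x − 5) and the SD is 2.5 × √0.75 = 2.17. The chance of an imputed PASI-50 is 0.24 for x = 7, 0.12 for x = 9 and 0.03 for x = 12. For 2 v 0 removals the shift falls from 2.7 points to between 0.24 × 2/30 = 1.6 and 0.03 × 2/30 = 0.2 points.

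**Against sampling error.** At 40% v 20% with 30 per arm, the standard error of the difference is √(0.24/30 + 0.16/30) = 11.5 points, a 95% half-width of about 23 points.

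**The case against.** **Direction.** A reader might infer that the rule overstates efficacy. The documents do not support that. Nothing says which arm will lose more participants, and the table shows zero or reversed shifts when the control arm loses enough more.

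**Size.** A reader might also treat the whole 15% as failure. At 40% v 20% that gives 0.34 − 0.17 = 17 points against 20, an overstatement of 3/17 = 17.6%. Section 5.9.1 describes the 15% as general loss to follow-up and does not tie it to adverse events or conversion. The marginal-rate formula is itself an upper-end case, because the protocol does not exclude earlier PASI from the imputation model. Section 5.9.2's restriction to baseline, week 8 and week 20 describes the comparison and does not clearly limit the imputation model.

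**Cause.** Not every removal is a treatment failure. A serious adverse event can be unrelated to treatment, and section 5.6.3 plans a causality assessment. Psoriatic arthritis is not in itself a failed skin response. Section 5.2 also withdraws participants who are unblinded, which says nothing certain about response. Some removed participants may have later assessments, so nothing would be imputed for them. After conversion, though, a later score may reflect the guideline treatment rather than the trial treatment.

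**Standing.** The aim in section 3.1 does not choose between the effect had nobody been removed and one that counts removal as failure. Non-response is a convention among defensible options. The affected outcomes are secondary, in a 60-participant pilot whose primary outcome is mean PASI change, and the full-scale trial may not use these rates. An analysis plan not available here could add a rule.

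These points limit direction, size and priority. They do not answer the gap: the protocol itself fixes one rule, that rule treats removal for worsening as ignorable, and no sensitivity analysis is stated.

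**Conclusion.** The point holds in a limited form. As written, section 5.9.2 allows a participant removed for another psoriasis type or a serious adverse event, and without a later assessment, to be counted as a PASI-50, PASI-75 or PGA responder. Relative to non-response, the response rate rises in each arm with such removals. Given a higher response rate on FZHFZY, the between-arm difference is inflated when such removals are balanced or fall more in the FZHFZY arm, and more exactly whenever dT/dC exceeds pC/pT. It is understated when they fall sufficiently more in the control arm.

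At 40% v 20% with one or two removals in an arm, the inflation is about 1 to 3 points where it occurs, and less if earlier PASI informs the imputation. That is well inside the pilot's sampling error. It rests on assumed response rates and removal counts, since the protocol gives neither. The change is worth making because it is cheap and removes an implausible classification, not because a large bias has been shown.

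**What to change.** In section 5.9.2, split the rule by reason for missingness.

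- For PASI-50, PASI-75 and PGA response, count a participant as a non-responder from the point of removal when removal is for conversion to another psoriasis type, a treatment-related adverse event, or documented lack of efficacy. The last is not a termination reason in section 5.5 and would arise only through voluntary withdrawal, so the reason must be recorded. Responses observed before removal stand.
- Apply the same status to the week-8 PASI-50 denominator for relapse, so that nobody removed earlier for these reasons enters it by imputation.
- Keep multiple imputation for all other missing values, and state that the model uses PASI from every visit.
- Add a sensitivity analysis that counts all serious-adverse-event removals as non-responders, whatever their cause. For PASI change, impute removed participants from the control arm or from their own baseline.

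The cost is a few sentences and a coded withdrawal reason in the case report form. Response rates become slightly less favourable. No participants or visits are added.
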